# Huatan Dingji Decoction intervening in atrial fibrillation: protocol for a randomized double-blind single-simulated placebo-controlled clinical trial

**DOI:** 10.1186/s13063-021-05522-z

**Published:** 2021-10-11

**Keywords:** Atrial fibrillation, Traditional Chinese Medicine, Huatan Dingji Decoction, Randomization double-blind single simulation

## Abstract

**Background:**

Atrial fibrillation (AF) is one of the most common cardiac arrhythmias and can lead to heart failure (HF), stroke, pulmonary embolism (PE), and other complications, seriously affecting people’s quality of life and health. Western medicine is limited in the treatment of AF, while Traditional Chinese Medicine (TCM) has unique advantages, such as less side effects, low toxicity, long effect duration, and high compliance. The prescription of HTDJ is a common prescription for the treatment of atrial fibrillation in Longhua Hospital, Shanghai University of Traditional Chinese Medicine. It has been used for many years and has a large number of clinically effective cases. It has a good clinical application prospect, but there is a lack of effective evaluation of its clinical efficacy.

**Method:**

This study adopts a randomized double-blind, single-simulated, placebo-controlled research method. Participants were randomly assigned in a 1:1 ratio through a centrally controlled, computer-generated, simple randomization schedule. Participants would take the medicine for 1 month, and the curative effect would be evaluated. Subsequently, the participants would not take TCM and only receive western medicine treatment. They would be followed up for another 8 weeks, and a clinical evaluation would be conducted. The secondary outcomes include echocardiography, Hamilton Anxiety Scale, Hamilton Depression Scale, rate of increase and decrease of anti-arrhythmia western medicine, the MOS 36-item short-form health survey, N-terminal-pro hormone B-type natriuretic peptide level, and integral TCM syndrome score. Adverse events will be monitored throughout the trial. Cases are from outpatient and inpatient with atrial fibrillation in the Cardiology Department of Longhua Hospital. Evaluations will be conducted at baseline and at weeks 4 and 12 after randomization.

**Discussion:**

In this study, the efficacy and safety of HTDJ plus western medicine in the treatment of atrial fibrillation (qi deficiency and phlegm opacities) will be evaluated, so as to provide medical evidence of short-term and medium-term clinical efficacy for the treatment of atrial fibrillation with integrated traditional and western medicine and lay a foundation for further clinical development and application.

**Trial registration:**

ClinicalTrials.govChiCTR2000030517. Registered on March 5, 2020, with the Chinese Clinical Trial Registry

## Introduction

Atrial fibrillation (AF) is a kind of supraventricular tachyarrhythmia characterized by rapid and disordered atrial electrical activity. It is one of the most common arrhythmias. It is estimated that approximately 2% of the global population has AF, and the incidence is increasing year by year, with a fivefold increase expected in the next 40 years [1]. AF can aggravate heart failure, increase the risk of ischemic stroke and malignant arrhythmia events, and increase the incidence with age, changes in heart structure and function, a variety of underlying diseases, bad living habits, etc., leading to increased hospitalization days, medical expenses, and overall mortality [2].

The current western medicine treatment for AF mainly includes drug therapy, left atrial appendage closure (LAAC), and radiofrequency ablation (RF). Pharmacotherapy, including cardioconversion of sinus rhythm and control of ventricular rate, should be used in combination with anticoagulant therapy. However, in the course of drug treatment of AF, most of the causes of AF cannot be removed, and the electrical and anatomical remodeling caused by AF itself makes it difficult to reverse AF and maintain sinus rhythm. Therefore, the control of ventricular rate has become a clinical alternative [3]. LAAC prevents thrombosis in the left atrial appendage during AF, thus reducing the risk of long-term disability or death due to thromboembolism in patients with AF. Radiofrequency ablation has become the most effective method for the radical treatment of paroxysmal tachyarrhythmia. Although radiofrequency ablation can restore sinuses in more than 70% of patients with paroxysmal AF, the long-term success rate is low, and the treatment of persistent or permanent AF is limited and ineffective [4, 5]. In recent years, through a large number of clinical studies, it has been found that TCM has unique advantages in the treatment of AF, such as less side effects, low toxicity, long effective duration, and high compliance, which has played a positive role and is widely used in clinical practice.

There is no name of AF in ancient TCM books. According to clinical symptoms and signs, AF should be classified as “palpitation,” and “shocking palpitation.” Since the book of “Huangdi Neijing” was published, doctors of different generations have discussed palpitation, and a variety of prescriptions have been recorded to be used for the treatment of palpitation, such as Zhigancao Decoction, Erchen Decoction, and Taoren Honghua Decoction. It is found that TCM has a certain curative effect in reducing ventricular rate, increasing cardioversion rate and improving cardiac function and its clinical symptoms [6]. [name], a professor of Shanghai Traditional Chinese Medicine in Longhua Hospital, has been engaged in various cardiovascular diseases including arrhythmia and AF for a long time. He has accumulated rich experience in clinical practice. The prescription of “Huatan Dingji Decoction”(HTDJ) for resolving phlegm and resolving palpitation is a prescription for the main syndromes of qi deficiency and phlegm opacities created by [name], one of his students, according to [name] academic idea, and combined with long-term clinical treatment experience. The whole recipe is composed of pinellia ginger, tangerine peel, astragalus root, atractylode rhizome, Poria, Coptis chinensis, cinnamon, keel, oyster, Radix ophiopogonis, Chinese date, Epimedium, and sophora flavescens. The prescription has a definite effect on the treatment of heart palpitation. A large number of related patients have taken this prescription for a long time, but it is limited to individual clinical cases and lacks a relevant evidence-based summary. Therefore, the purpose of this study was to evaluate the efficacy and safety of “HTDJ” in the treatment of AF with western medicine, to provide evidence-based medical evidence of short-term and medium-term clinical efficacy of integrated Chinese and Western medicine in the treatment of AF on the basis of TCM syndrome differentiation, and to lay a foundation for further clinical development and application.

## Methods/design

### Study objectives

The purpose of the experiment is to evaluate the efficacy and safety of HTDJ plus western medicine in the treatment of atrial fibrillation, provide medical evidence of short-term and medium-term clinical efficacy for the treatment of atrial fibrillation with integrated traditional and western medicine on the basis of TCM syndrome differentiation, and lay the foundation for further clinical development and application.

### Study design and settings

We designed this study as a randomized, double-blind, single-simulated placebo-controlled clinical trial. The study will be conducted in the Department of Cardiology, Longhua Hospital, Shanghai University of Traditional Chinese Medicine, to achieve the goal of 76 participants with atrial fibrillation (qi deficiency and phlegm opacities) in total. The participants who fulfill both the inclusion and exclusion criteria will be recruited into the study. After participants signed the consent form, they will be randomly assigned to the treatment or control group. Participants in the treatment group will receive HTDJ, whereas those in the control group will receive placebo granules. The participants will continue to receive systemic therapy, as judged by their treating physician. All changes in symptoms, prescriptions, relevant scores, and macroscopic characteristics (based on photographic evidence), along with any adverse events (AEs), will be recorded. The experimental design is shown in Fig. 1.

**Fig. 1 Fig1:**
[figure not shown]
Trial flow chart

### Eligibility criteria

Eligible patients will be those who fulfill all of the following inclusion criteria and who do not have any of the listed exclusion criteria. The planned enrollment period is 12 weeks.

### Diagnostic criteria

The diagnosis of atrial fibrillation can be confirmed based on clinical manifestations, physical examination, and electrocardiographic characteristics as follows [7]: (1) clinical manifestations: palpitation, chest tightness, and decreased exercise tolerance; (2) physical examination: heart auscultation varies in the heart rate, and heart sounds vary in strength, rhythm is absolutely irregular, and pulse is short; and (3) electrocardiogram: *P* wave disappear, the *f* wave replaces it, the frequency is about 350–600 times, and the QRS complex rhythm is absolutely irregular.

### Inclusion criteria

The inclusion criteria are as follows: (1) The patient’s age is 18–85 years; (2) atrial fibrillation, seizure frequency ≥2 times a month (at least one ECG diagnosis); (3) the main syndrome of TCM syndrome differentiation was Qi deficiency-caused phlegm stagnation; and (4) have a correct understanding of the significance of the study, have good compliance with the observation and evaluation of the researcher, and voluntarily accept the clinical trial and fill in the clinical consent form.

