### Outcomes

#### Primary outcome

Frequency of atrial fibrillation attacks (from baseline to weeks 4, 8, and 12)
° Significant effects: The frequency of attacks decreased by more than 70%.° Effective: The frequency of attacks decreased between 30% and 70%.° Invalid: The frequency of attacks decreased by less than 30%.° Deterioration: Increased attack frequency.

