### Research process record points

The subject content and data at each time point, according to the patient’s hospitalization period, will be recorded as shown in Table 1. Specifically, the screening period (−3~0 days) will be 0 to 3 days before recruitment. The 4-week treatment period was planned in two cycles of 2 weeks, with a return visit between cycles to check for AEs and monitor compliance. All interventions will be stopped after 4 weeks. Follow-up will be conducted on weeks 4 and 12. The detailed information is shown in Table 3.

**Table 3 Tab3:** Research flowchart

Activity	Phase(time points)	Screening stage	baseline period	intervention	Follow-up	
		−3d~0d	0d	4w	8w	12w
**Enrolment**	Sign informed consent	✔				
	Inclusion and exclusion criteria	✔				
	Demographic data	✔				
	Medical history and treatment history	✔				
	Basic data collection	✔				
**Outcome assessment**	Frequency of atrial fibrillation		✔	✔	✔	✔
	ECG and Holter		✔	✔	✔	✔
	Ultrasonic cardiogram		✔	✔	✔	✔
	TCM clinical syndrome integral		✔	✔	✔	✔
	Rate of increase and decrease of anti-arrhythmia western medicine		✔	✔	✔	✔
	NT-proBNP		✔			✔
	Hamilton Anxiety Scale		✔	✔	✔	✔
	Hamilton Depression Scale		✔	✔	✔	✔
	SF-36		✔	✔	✔	✔
	PVO		✔	✔	✔	✔
	Anaerobic threshold		✔	✔	✔	✔
**Safety assessment**	Physical examination		✔	✔	✔	✔
	Blood routine examination		✔	✔		
	Urine routine and urinary sediment		✔	✔		
	Liver function		✔	✔		
	Renal function		✔	✔		
	Blood lipid		✔	✔		
	GLU		✔	✔		
	INR		✔	✔		
	CHA2DS2-VAS		✔	✔		
	HAS-BCED		✔	✔		
**Other information**	Randomization	✔				
	Hemorrhage		✔	✔	✔	✔
	Readmission		✔	✔	✔	✔

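### The primary grades use only the fall in attack count, so a participant whose AF becomes continuous during follow-up can be graded a responder

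*Protocol article*

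**What the plan says.** All from the protocol article.

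- **Inclusion criteria:** "atrial fibrillation, seizure frequency ≥2 times a month (at least one ECG diagnosis". Neither this criterion nor the diagnostic criteria name an AF type.
- **Primary outcome:** "Frequency of atrial fibrillation attacks (from baseline to weeks 4, 8, and 12". There are four grades. *Significant effects* is "The frequency of attacks decreased by more than 70" percent, *Effective* is "The frequency of attacks decreased between 30% and 70" percent, and *Invalid* is "The frequency of attacks decreased by less than 30" percent. The last is "Deterioration: Increased attack frequency". No grade refers to episode duration, AF burden or rhythm at the visit.
- **Research process record points, Table 3:** "ECG and Holter" is listed under outcome assessment at baseline and weeks 4, 8 and 12, the same time points as the attack frequency. The article does not say how these recordings enter the grade.
- **Criteria for discontinuing or modifying allocated interventions:** if the disease worsens, stopping is left to the doctor's judgment. The last main efficacy result is then used as the final one. The clause mentions invalid cases but does not clearly tie worsening to a primary-outcome grade.

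**The concern.** A count of attacks measures disease activity only while attacks start and stop. Once AF no longer terminates, there are few or no new onsets to count, and the count falls because the rhythm has worsened. The grades as printed read that fall as benefit, and the only route to *Deterioration* is a higher count.

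The Introduction makes this course plausible. It says that remodelling caused by AF makes sinus rhythm hard to maintain, and it distinguishes paroxysmal from persistent or permanent AF.

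At stake is the meaning of the primary response rate. Some failures could be counted as successes, and if progression differs between arms, the comparison is distorted as well.

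**Working it through.** **Step 1. Grade after progression.** The protocol states no figure for this, so the check applies its own grading rule. Inputs are baseline count *b* ≥ 2 a month (Inclusion criteria) and the grade limits of 30% and 70% (Primary outcome). Two assumptions are mine: baseline and follow-up windows are of equal length, and an unbroken episode gives *k* = 0 (no new onset) or *k* = 1 (the episode itself).

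Percent fall = (*b* − *k*)/*b* × 100.

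| Baseline *b* | Fall if *k* = 1 | Grade | Fall if *k* = 0 | Grade |
|---|---|---|---|---|
| 2 | 50% | Effective | 100% | Significant effects |
| 3 | 66.7% | Effective | 100% | Significant effects |
| 4 | 75% | Significant effects | 100% | Significant effects |
| 6 | 83.3% | Significant effects | 100% | Significant effects |
| 10 | 90% | Significant effects | 100% | Significant effects |

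The smallest fall for any *b* ≥ 2 is (2 − 1)/2 = 50%. Under either count, *Invalid* and *Deterioration* cannot occur. One limit applies: in the window where the change happens, terminated attacks before it also count, so *k* may exceed 1 there. The result applies to windows with a count of 0 or 1, which under these conventions includes every later window in which AF stays continuous.

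**Step 2. Does the discontinuation section prevent this?** Not reliably. Stopping is discretionary. If the last efficacy result was taken after AF became continuous, the favourable grade is the one carried forward.

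**Step 3. Weight of one participant.** The Sample size section gives 30 per group and 76 in total: 30/(1 − 0.20) = 37.5, rounded up to 38 per group, and 2 × 38 = 76. One misgraded participant moves an arm's rate by 1/38 = 2.6 points, or 1/30 = 3.3 points.

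**Step 4. Illustration of the comparison.** The documents give no progression rate, so every rate below is an assumption. Planned response rates are 91.1% and 53.3% (difference 37.8 points), with margin 10%, α = 0.025 taken as one-sided, and 30 per arm. All progressors are taken from would-be non-responders, which is the extreme case.

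Chance of showing superiority = Φ[(p₁ − p₂ − 0.10)/SE − 1.96], with SE = √{[p₁(1 − p₁) + p₂(1 − p₂)]/30}.

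With none misgraded: SE = √[(0.0811 + 0.2489)/30] = 0.1049; 0.278/0.1049 − 1.96 = 0.69; Φ = 75.5%.

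| Misgraded, HTDJ / control | Rates used | Difference | Chance of showing superiority |
|---|---|---|---|
| 0% / 0% | 0.911, 0.533 | 37.8 | 75.5% |
| 5% / 5% | 0.961, 0.583 | 37.8 | about 82% |
| 5% / 10% | 0.961, 0.633 | 32.8 | 67.2% |
| 5% / 15% | 0.961, 0.683 | 27.8 | 49.0% |
| 5% / 0% | 0.961, 0.533 | 42.8 | about 92% (0.328/0.0977 − 1.96 = 1.40) |

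The sign of the effect depends entirely on which arm is assumed to progress more. Equal rates leave the difference unchanged.

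**The case against.** The strongest objection is that the article never says what an attack is or how an unbroken episode is counted. That definition may stand in the full protocol, the case report form or the analysis plan. If AF were counted in days or recordings with AF, the reversal would disappear. This stands as a limit: the 0 or 1 count is an assumption. It does not remove the point, because the printed grades know only a change in frequency, and both natural ways of counting episodes give a responder grade.

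Three stronger readings are tempting, and the document does not support them.

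- *The trial ignores AF type at entry.* No type is named, but requiring at least two attacks a month in effect selects recurrent, countable episodes. The weakness lies in the grading of follow-up.
- *ECG and Holter are collected but unused.* Table 3 puts them under outcome assessment beside the attack frequency, so they may well serve to ascertain attacks. Silence in a condensed article does not show otherwise.
- *The comparison is biased towards one arm.* Without progression rates, neither size nor direction can be stated. Illustrations with more progression on control only would mislead.

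It is also fair that the discontinuation section addresses worsening and uses the word invalid, which is also the label for non-response. The wording is too ambiguous to be relied on as a grade.

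**Conclusion.** The point holds in a limited form. As printed, the primary grading has no way to record a change to continuous AF as worsening. With an eligible baseline and a follow-up count of 0 or 1, it grades that course *Effective* or *Significant effects*. This rests on the assumed count and on comparable windows.

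How often it would happen in 12 weeks is unknown, and so is any imbalance between arms. What can be stated is the weight of each case, 2.6 to 3.3 points on an arm's response rate. The grading should be corrected because it can score worsening as success and the remedy is cheap. The documents do not show that the trial's result would be wrong.

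**What to change.** Add to the grading under Primary outcome: a participant who is in AF on the visit ECG and throughout the visit Holter, with no return to sinus rhythm recorded or reported since the previous scheduled outcome visit, is not counted as a responder and is graded *Deterioration* whatever the attack count; this is assessed blind to arm. Report Holter-recorded AF at weeks 4, 8 and 12 as a supportive outcome. If the full protocol already says how unbroken AF is counted and graded, state that rule here instead.

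Requiring AF across the whole interval matters. A rule based on the visit recordings alone would grade as *Deterioration* someone whose attacks had fallen to a single recent episode that had not yet ended.

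The cost is two sentences and no new procedure, since ECG and Holter are already scheduled at every outcome visit. The response rate may be slightly lower. An occasional long episode will be misclassified, for instance when a brief return to sinus rhythm went unnoticed. AF that becomes continuous partway through the last interval will not be caught at week 12. This changes only the outcome definition, not the management of participants.

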### Exclusion criteria

The exclusion criteria are as follows: (1) patients with primary diseases such as severe lung, liver, renal insufficiency, and hematopoietic system or severe cardiac dysfunction (NYHA IV grade); (2) atrial fibrillation caused by obvious incentives such as fatigue, mental stress, mood swings, drug poisoning, and electrolyte disturbance; (3) mental illness and poor control of the condition; (4) patients whose heart rate is less than 50 beats per minute (such as sick sinus syndrome, atrioventricular, or intraventricular block, who intend to install a pacemaker); (5) pregnant or lactating women; (6) cachexia in the terminal stage of malignant tumor; and (7) for various reasons, the efficacy cannot be determined or the data is incomplete.

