### Criteria for discontinuing or modifying allocated interventions

The criteria for discontinuation are as follows: (1) In case of serious adverse events, the clinical experimenter should be stopped according to the doctor’s judgment. (2) If the disease worsens in the course of the disease, or there are other conditions affecting the observation of the study, the clinical experimenter should be stopped and invalid cases should be treated according to the doctor's judgment. (3) Important deviations occurred in the implementation of clinical trial protocols, such as poor compliance, making it difficult to evaluate drug effects. (4) The subject is unwilling to continue the clinical trial during the clinical trial and proposes to the doctor in charge to withdraw from the clinical trial.

For these cases, the reasons for discontinuation shall be recorded in detail. If there is a review, the results of the last major efficacy test shall be taken as the final results for statistical analysis, and the CRF table and REDCap (Research Electronic Data Capture) shall be kept for future reference.

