### Sample size

The sample size of this study was calculated based on the analysis of data published in previous articles on the treatment of atrial fibrillation by Chinese medicine and the expected value of efficacy. It was assumed that the total efficacy rates in the study and control groups were 91.1% and 53.3%, respectively [8]. The set *α* = 0.025, *β* = 0.2, superiority limit value*δ*= 10%, and the sample size of each group will be calculated as 30 cases, considering a 20% loss to follow-up, that is, a total of 76 cases.

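### Exclusion criterion 7 depends on outcome data normally unknown before randomisation, and it conflicts with the carry-forward rule for discontinued participants who had a review

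*Protocol article*

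**What the plan says.** **Exclusion criteria, item 7.** A patient is excluded if "for various reasons, the efficacy cannot be determined or the data is incomplete". The item does not say when it is applied or which data are meant.

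**Eligibility criteria** and **Study design and settings.** The list is presented as an entry screen. Eligible patients are those "who do not have any of the listed exclusion criteria", and "The participants who fulfill both the inclusion and exclusion criteria will be recruited into the study". Consent and allocation come afterwards.

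**Criteria for discontinuing or modifying allocated interventions.** Reasons for stopping include serious adverse events, worsening, withdrawal, and important protocol deviations "such as poor compliance, making it difficult to evaluate drug effects". For these cases, on condition that there was a review (a term the article does not define), "the results of the last major efficacy test shall be taken as the final results for statistical analysis". Nothing is said about cases without a review.

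**Primary outcome.** Change in attack frequency from baseline to weeks 4, 8 and 12, in four grades. Treatment ends at week 4.

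**Sample size.** The calculation assumes that "the total efficacy rates in the study and control groups were 91.1% and 53.3%, respectively". It arrives at 30 per group and then inflates, "considering a 20% loss to follow-up, that is, a total of 76 cases".

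**The concern.** Efficacy here is a change from baseline measured at weeks 4, 8 and 12, so whether it can be determined is normally unknown on the day of randomisation. An exclusion that depends on it would, if applied literally, operate after randomisation and select participants by whether their outcome was obtained. The protocol's own reasons for stopping include worsening and serious adverse events, so missing outcomes may well be related to response or tolerability. Excluding such people then no longer compares the groups as randomised.

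The discontinuation section points the other way for some of the same people, because it keeps them with their last result. That rule has its own weakness. Study treatment ends at week 4 and the article aims at medium-term efficacy, yet a good week-4 result could stand in for week 12 in someone who relapsed and left.

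**Working it through.** **1. The two rules side by side**

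| Participant | Criterion 7 read literally | Discontinuation section |
|---|---|---|
| Completes all assessments | not affected | not affected |
| Discontinued, had a review, later data incomplete | excluded | last result used as final |
| Discontinued, no review | excluded | no rule |
| Not discontinued, but data incomplete | excluded | no rule |

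Only the second row is a direct contradiction. In the third and fourth, criterion 7 is the only text that could apply. The poor-compliance reason for stopping, where the drug effect is hard to evaluate, is close in meaning to criterion 7, so the overlap is a realistic one.

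**2. How many people this could concern**

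Inputs from Sample size: 30 per group, 20% loss. 30 / (1 − 0.20) = 37.5, rounded up to 38; 2 × 38 = 76. The plan's loss allowance reproduces. It implies 38 − 30 = 8 per arm, 16 in all. The 30 is taken as given here; its derivation is a separate matter.

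**3. Bias from excluding incomplete cases when there is no true effect**

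Assumptions: true response rate p = 0.533 in both arms (the plan's control rate) and about 20% loss in each arm, with control losses unrelated to outcome. Let dR and dF be the dropout proportions among responders and failures in the HTDJ arm. The response rate among those kept is

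r = p(1 − dR) / [p(1 − dR) + (1 − p)(1 − dF)]

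and the bias is r − 0.533. The dropout patterns are illustrative and are not in the article.

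| HTDJ-arm dropout | dR | dF | r | Bias |
|---|---|---|---|---|
| Unrelated to outcome | 0.20 | 0.20 | 0.533 | 0 |
| Mainly failures | 0.10 | 0.314 | 0.4797 / 0.8001 = 0.600 | +6.7 points |
| Only failures | 0 | 0.428 | 0.533 / 0.8001 = 0.666 | +13.3 points |
| Mainly responders | 0.30 | 0.086 | 0.3731 / 0.7999 = 0.466 | −6.7 points |

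The same worst case in whole participants: 38 × 0.533 = 20.3 responders. Removing 8 non-responders gives 20.3 / 30 = 67.5%, or +14.2 points. Removing 4 gives 20.3 / 34 = 59.6%, or +6.3 points. The small gap between 13.3 and 14.2 arises because 8 of 38 is 21.1%, not 20%.

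**4. How far the handling rule moves the result if the planned rates are true**

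Take 27/30 and 16/30 responders among completers (close to 91.1% and 53.3%) and 8 dropouts per arm.

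- Dropouts excluded: 90.0% − 53.3% = 36.7 points.
- All dropouts counted as non-responders: 27/38 − 16/38 = 71.1% − 42.1% = 28.9 points.
- Extremes: 27/38 − 24/38 = 7.9 points; 35/38 − 16/38 = 50.0 points.

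**5. Carry-forward**

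The article gives no relapse rate, so a total cannot be computed. Each participant wrongly carried as effective to week 12 adds 1/38 = 2.6 points to that arm's rate.

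**The case against.** The strongest defence is that criterion 7 sits in a list of eligibility criteria applied before consent and allocation. A pre-entry meaning is available: if baseline attack frequency cannot be established, a percentage change can never be calculated. This stands in part. A reader might infer that the protocol orders the removal of randomised participants, but no text says so; that is the effect of a literal application. The defence does not rescue the wording, because nothing in the item limits it to baseline data and inclusion criterion 2 already requires a known attack frequency.

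Second, the two rules may be complementary: with a review the last result is used, and without one efficacy cannot be determined. This also stands in part. It confines the direct conflict to discontinued participants who had a review but whose later data are incomplete. A reader might suppose that someone who stops before week 4 with no review is carried forward from baseline and graded as invalid. The carry-forward rule requires a review, so it does not cover that case. Nor does stopping poor compliers mean dropping them from the analysis: with a review, their last result is kept.

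Third, the discontinuation section concerns the allocated interventions, and these end at week 4. Whether it governs someone who leaves during untreated follow-up is not fully clear, although its items on worsening and on withdrawal from the trial can be read that way. The relapse example rests on that reading.

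Fourth, the +14 points can be mistaken for an expected bias. It requires every loss in one arm to be a non-responder and no selective loss in the other. Equal selective loss in both arms, with equal true rates, gives no bias. Nor is a shift in a point estimate directly comparable with the 10-point margin, which is judged by a confidence limit.

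Finally, a reader might conclude that the analyst is free to choose a rule after seeing the data. The full protocol and any SAP are not shown and may define the analysis sets, so that conclusion is not supported. What remains is the conflict in the wording that is shown.

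**Conclusion.** The point holds in a limited form. Criterion 7 is placed as an entry criterion but is worded around information normally available only after treatment. It conflicts with the discontinuation section for participants who stopped, had a review and have incomplete later data. For those without a review it is the only text that could apply. Carry-forward is a weak rule for a trial that stops treatment at week 4 and evaluates at week 12.

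The bias is conditional on informative dropout, and its direction cannot be known in advance. With no true effect it ranges from 0, through about ±6.7 points under moderate one-arm selection, to about +13 to +14 points in the one-arm worst case. These figures assume the plan's 20% loss and 53.3% control rate together with illustrative dropout patterns. The bias from carry-forward is not quantified beyond 2.6 points per misclassified participant.

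**What to change.** 1. Delete criterion 7, or limit it to facts known before randomisation, for example that baseline attack frequency cannot be established.
2. State that all randomised participants are analysed in their assigned arm.
3. Seek the week 4, 8 and 12 outcomes after treatment discontinuation, including in poor compliers, wherever the participant has not withdrawn from the trial.
4. Replace last-value-carried-forward as the primary rule with one prespecified missing-data method, for example multiple imputation. Report non-response imputation and complete-case results as sensitivity analyses.

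Whether stopping for worsening or a serious adverse event should count as non-response in the main analysis is a choice of estimand. The sponsor should make it explicitly, but this point does not depend on it.

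The cost is a change of wording, slightly more analysis work and some added follow-up effort. The last is more than an editorial matter, because recruitment began in April 2020 and outcomes not collected so far may be irrecoverable. The reported response rate may also look less favourable.
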